#### Retention

The retention rate will assess the proportion of participants who complete the study compared to those who were initially recruited. A high retention rate is key to ensuring the validity of the results. It is calculated by dividing the number of people who completed the intervention by the total number of individuals enrolled at the start [70].

#### Fidelity

Fidelity involves assessing participants’ responses as a result of the practices used to ensure that the responses reliably and validly represent the purpose of the intervention. It will be evaluated through checklists in each session with the following criteria: attention, positive attitude, active participation, work in the sessions, and attendance lists [27].

#### Acceptability

Acceptability will be assessed by measuring perception and satisfaction at the end of the intervention, analyzing aspects such as effectiveness, motivation, barriers, and limitations, which will allow for obtaining feedback to improve the design of future studies. To evaluate the social aspect of the program’s acceptability, participants will be given a survey with both open-ended and multiple-choice sections using a Likert scale [32,71-73].

### Statistical Analysis

The normal distribution of the data will be verified using skewness, kurtosis, and Kolmogorov-Smirnov tests. Quantitative data with nonnormal distribution will be mathematically transformed for parametric analysis, or alternatively, nonparametric analysis will be used. Means and SDs will be calculated for continuous variables and percentages for categorical variables. To test age, sex, socioeconomic status, and location baseline differences, we will use chi-square tests for qualitative demographic variables (eg, socioeconomic level, family medical history, sport practice, etc) and analysis of covariance for quantitative variables (eg, anthropometrics, dietary intakes, HEI, TMexD, sleep time, BIP, family interaction, and psychosocial well-being). To evaluate specific aim 1, potential baseline associations of dependent variables (eg, anthropometrics and blood pressure) with independent behavioral variables (eg, dietary intakes, exercise and sleep time, family interaction, psychosocial well-being, and perception of childhood obesity) will be tested using multiple linear regression, starting with univariate regression (*P*<.2 and biological plausibility). Models will be built by a combination of univariate analysis and forward stepwise model selection using *P*≤.05 and biological plausibility. Preliminary models will be assessed for possible interactions (*P*≤.1) between sex and other variables included in the model, for collinearity (variance inflation factor<10), and for linear regression assumptions (linearity, normality, and homoscedasticity) using residual plots. Specific aim 2 will use mixed methods (qualitative and quantitative) to analyze results in terms of retention, fidelity, and acceptability of the intervention by children and school administrators. Specific aim 3 will compare the changes between the experimental arms (intervention vs control) from baseline to postintervention and to the 6-month follow-up in anthropometrics, blood pressure, HEI, dietary intakes, PA, sleep time, and knowledge. Primary analyses will follow the intention-to-treat principle. Given the hierarchical structure of the data (students nested within classrooms and classrooms within schools) and the repeated measurements over time (baseline, postintervention, and 6-month follow-up), intervention effects will be evaluated using multilevel mixed-effects regression models. Due to the cluster-based allocation, the intraclass correlation will be considered, potential attrition will be monitored, and all analyses will account for clustering to provide valid inferences. Models will include fixed effects for study arm, time, and the arm×time interaction, and random effects for classroom and school to account for intracluster correlation. Baseline values of the outcomes and covariates will be included as appropriate. Effect estimates with 95% CIs will be reported. We will examine model assumptions and fit indices. SPSS (IBM SPSS Statistics version 21.0) and STATA (StataCorp version 14.0) software will be used, with a *P* value <.05 for all statistical analyses.

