### Selection of Schools

The districts and neighborhoods with the lowest economic resources in the region were identified using socioeconomic census data from the National Institute of Statistics and Geography (INEGI, for its acronym in Spanish), and 4 elementary schools were selected according to logistical feasibility and resources: 1 in Loma de Bácum (representing the rural area) and 3 in Ciudad Obregón, Sonora, México (representing the urban area). An interview will be held with the school principals to present the proposal, and those who agree will be asked for written authorization. Within each school, an equal number of groups (classrooms paired by grade) will be selected for the intervention and control arms, allowing for approximate matching of participants by sex and age in each arm. This approach allows us to offer the program to at least half of the students in each school and to implement the intervention in as many schools as possible according to available resources.

The number of classrooms per school is determined by the existing school structure and logistical feasibility. Across the 4 schools, a total of 24 classrooms will be included (12 in the intervention arm and 12 in the control arm), with varying numbers of students (participants) per classroom, since student grouping is pre-established by the Ministry of Education at the beginning of the school year.

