The study’s conceptual model in Figure 2 posits that the intervention influences outcomes indirectly through internal processes and individual factors. Mediating variables such as BIP and adherence to the TMexD, among others, strengthen personal and social resources, thereby facilitating the adoption and maintenance of healthy habits. Moderating variables (such as sex and location, etc) shape the context in which these changes occur and potentially influence how individuals interpret, assimilate, and respond to the intervention, ultimately modulating observed outcomes.

Regarding child nutrition, Bujtor et al [76] identified that unhealthy dietary patterns high in fat and sugary drinks were associated with impaired body composition and inflammatory biochemical parameters (ie, inflammatory cytokines, C-reactive protein, total cholesterol, triglycerides, glucose, and insulin) [77]. Likewise, healthy dietary patterns (ie, those rich in fruits and vegetables and low in UPF and sugary beverages) should be promoted from early childhood, given that children tend to exhibit greater food selectivity. With respect to PA patterns, studies reported that almost 50% of children and adolescents usually spend more time in sedentary activities (ie, screen time), consuming more sugary and salty foods, with an increase in weight and body fat [15,78]. On the contrary, an active PA pattern is associated with improvements in adiposity [79], self-esteem, mental health [80], quality of life, cognitive abilities, academic performance, etc [81]. Even low-intensity PA promotes favorable health changes in children and young people with obesity [1].

As reported by Heggmen and Zahl [82], children from rural communities have a higher risk of overweight, obesity, and unhealthy habits. Some causes include limited access to healthy foods, less space availability for PA, and less nutrition and health education. However, children from urban communities are also at risk of obesity due to their social environment: globalization, modernization, cultural changes, and low economic conditions [74]. This proposal includes participants from rural and urban communities and schoolchildren from mestizo and indigenous origins, ensuring equity, cultural relevance, and social justice, reducing the gap and improving external validity due to participants’ diversity [25-27].

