Among the strengths are its reach and accessibility, as it was conducted in schools where children spend a lot of time, representing a realistic and ideal environment for a large number of participants, with a lower probability of withdrawal. School age represents a critical growth period in the formation of lasting habits, and children can be multiplying intervention agents in their families. Another strength is the involvement of rural and urban schools, which promotes equity and reduces the disparity in cardiometabolic risk between both communities. The experimental design using school groups as units optimizes resources and allows for a larger number of schools to be intervened. Another advantage is the comprehensive approach for assessing family habits such as adherence to the TMexD and psychosocial variables. Individual variables such as diet, sleep, and PA times are fundamental in lifestyle habits, and evaluating the intervention in terms of feasibility, viability, retention, and acceptability allows measurement of the sustainability of acquired skills over time. Regarding the use of repeated-measures ANOVA, this is a robust tool in this type of study evaluating participants at multiple times.

Among the limitations, classrooms were randomized within schools, which, while not the optimal design for this type of study, enabled us to offer the intervention to more participants in each school. Logistical and funding constraints limit a second-year waiting-list control design, leading us to prioritize implementation across multiple schools. School schedules (eg, recess, arrival, and dismissal) are structured to minimize interaction between classrooms, reducing the likelihood of contamination. Nevertheless, we acknowledge that some contamination may occur and will address this with appropriate statistical analyses. Another limitation is the relatively low sample size for this kind of study, since this type of design requires a larger number of participants and the use of robust statistical methods. However, our research design is comparable to similar studies [74].

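### Baseline location tests compare one rural school with three urban ones, so a rural-urban P value cannot be attributed to rurality and, read that way, exceeds its 5% error rate if schools differ at all

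*Protocol article*

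**What the plan says.** Selection of Schools fixes the geography: "1 in Loma de Bácum (representing the rural area) and 3 in Ciudad Obregón, Sonora, México (representing the urban area"). The four were chosen from the poorest districts on grounds of feasibility and resources.

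Statistical Analysis plans: "To test age, sex, socioeconomic status, and location baseline differences, we will use chi-square tests" for qualitative variables, and "analysis of covariance for quantitative variables" such as anthropometrics, diet, sleep and psychosocial scores. The Abstract repeats the plan and makes clear that location is a grouping factor by which baseline values are compared.

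Further on, among the models for the intervention effect, the same section promises that clustering will be taken into account in every analysis, and it gives those models random effects for classroom and school. No cluster term is attached to the chi-square tests or the analysis of covariance.

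The Discussion, describing the conceptual model, says: "Moderating variables (such as sex and location, etc) shape the context in which these changes occur". It counts the mix of rural and urban schools as a strength. Its limitations do not mention that only one school is rural.

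**The concern.** Every rural child attends the same school. Whatever sets that school apart (its staff, canteen, intake, or the days on which it was measured) is therefore part of the location contrast, and no model can split it off.

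A child-level test nevertheless treats the 451 children as independent units on the two sides of a rural-urban line, when there is one school on one side and three on the other. At stake are the baseline P values for location. The planned list of baseline variables is long, so the inflated error would recur across many tests, and a difference between schools could be reported as a difference between rural and urban children.

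**Working it through.** **Inputs from the article.** Schools: 1 rural, 3 urban (Selection of Schools). School sizes: 173, 117, 86, 75 (Table 3). Significance level: 0.05 (Statistical Analysis), taken here as two-sided.

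**Assumed.** The between-school ICC, ρ, is not given, so a range is shown. Table 3 does not say which school is rural, so each is taken in turn.

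**The article's own figure.** 173 + 117 + 86 + 75 = 451, which matches the stated total.

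**Formulas** (total variance 1; n_r children in the rural school, n_j in each urban school, N_u urban children in all):

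- Variance assumed by a child-level test: V0 = 1/n_r + 1/N_u
- Variance with a school effect: V = ρ(1 + Σn_j²/N_u²) + (1 − ρ)V0
- Actual type I error = 2[1 − Φ(1.96/√(V/V0))]

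**Largest school rural, ρ = 0.01.** N_u = 117 + 86 + 75 = 278. Σn_j²/N_u² = 26,710/77,284 = 0.3456. V0 = 1/173 + 1/278 = 0.00938. V = 0.01 × 1.3456 + 0.99 × 0.00938 = 0.02274. V/V0 = 2.42 and 1.96/√2.42 = 1.26, so the error is 20.8%.

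**Smallest school rural, ρ = 0.01.** N_u = 376. Σn_j²/N_u² = 51,014/141,376 = 0.3608. V0 = 1/75 + 1/376 = 0.01599. V = 0.01 × 1.3608 + 0.99 × 0.01599 = 0.02944. V/V0 = 1.84, so the error is 14.9%.

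| Assumed school ICC | V/V0, range over which school is rural | Actual type I error |
|---|---|---|
| 0 | 1.00 | 5% |
| 0.005 | 1.42-1.71 | 10.0-13.4% |
| 0.01 | 1.84-2.42 | 14.9-20.8% |
| 0.02 | 2.68-3.85 | 23.1-31.8% |
| 0.05 | 5.20-8.12 | 39.0-49.2% |

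Simulation (10,000 runs each, smallest and largest school as the rural one) agrees. At ICC 0.01 the t-test gave 15.0-20.8% and the chi-square test 14.9-21.1%. At ICC 0.05 they gave 39.7-50.0% and 39.5-50.6%. The chi-square runs used a prevalence of 37.3%, the Introduction's figure for overweight and obesity in schoolchildren.

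**If clustering is honoured.** With the school as the unit there are 4 − 2 = 2 degrees of freedom, and the critical t is 4.30 instead of 1.96. In simulation at ICC 0.01 to 0.05 this test holds its error at 4.3-5.9%, but only by borrowing the between-school variance from the three urban schools. The smallest possible permutation P is 1/4 = 0.25. At ICC 0.01, with about 110 children per school, 80% power needs a difference of about 0.9 SD. Even then the rural side rests on one school.

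**The case against.** **The plan already promises to allow for clustering.** It does, and the unadjusted child-level reading is therefore not settled. But the promise stands with the intervention-effect models and does not fit the plain tests named for baseline, so the two statements conflict. Honouring it corrects the standard error and leaves the confounding in place.

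**The error rates depend on the ICC and on the target.** This stands in part. A reader might infer that the tests are bound to produce false differences. The article does not support that, because it gives no ICC, and at ICC 0 the error is 5%. The formula is also for an unadjusted two-group comparison, and covariates in the analysis of covariance could change the residual ICC. If the question is only how children in these four schools differ, a child-level test has no school-sampling inflation. The fault then lies in labelling the difference as rural-urban.

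**Location as moderator is theory, not a planned test.** This stands. A reader might infer that a test of moderation by location is planned. Statistical Analysis states no arm-by-location term; the only interactions it screens are "possible interactions (*P*≤.1) between sex and other variables included in the model", in the baseline association models. Likewise, the statement that including both settings "promotes equity and reduces the disparity in cardiometabolic risk between both communities" is an optimistic remark about reach and does not report a test.

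**The point is peripheral.** It is limited. None of the three specific aims rests on a location comparison, and classrooms are paired and randomised within each school, so the arm comparison is not confounded by location.

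**Conclusion.** The point holds for the baseline location comparison. That location coincides with one school follows from the design alone and needs no assumption. The size of the error does need assumptions: the schools stand for wider rural and urban populations, the test is two-sided and unadjusted, and the school ICC is above 0. On those terms a nominal 5% test has a false-positive rate of 15-21% at ICC 0.01 and 39-49% at 0.05.

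A reader might go further and infer that the trial's main result is compromised. The document does not support this, because allocation was within school. If an arm effect were compared between locations it could be estimated, but the difference could not be attributed to rurality.

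**What to change.** 1. Drop location from the factors tested at baseline, in both the Abstract and Statistical Analysis. Report baseline values by school with confidence intervals and no location P value, and label them as differences between these schools.
2. Reconcile the sentence naming chi-square and analysis of covariance with the promise that every analysis allows for clustering.
3. State the single rural school among the limitations in the Discussion.
4. If arm effects are shown by location or school, call the variation between-school heterogeneity and not moderation by rurality.

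Taking location out of the conceptual model, or softening the equity statement, is optional. The cost is wording only: the trial gives up a rural-urban inference that its design cannot support. Table 3 shows data analysis ticked for two of the four schools and interpretation for none, so the change can still be made before results are interpreted.

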### Participants

The inclusion criteria are being students aged 6 to 13 years enrolled in the selected schools, with availability to complete the intervention; residents of either Ciudad Obregón and/or Valle del Yaqui, Sonora; and having informed consent from a parent or guardian. The exclusion criteria are having any physical, metabolic, or mental illness that prevents them from carrying out the intervention or undergoing a health intervention program or diet, exercise, lifestyle, and/or therapeutic treatment in the 3 months prior to the study. Data collection instruments, questionnaires, and intervention activities were tailored for lower (children aged 6‐9 years, up to grade 3) and upper (children older than 9 years in grades 4 to 6) elementary school groups. For all school groups, a staff member acted as a support interviewer in the application of instruments and questionnaires.

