### Blood Pressure

The procedure will follow the NOM-030-SSA2-2009 [44] using a portable digital OMRON HEM-7120 blood pressure monitor. Measurements will be taken in triplicate on the left arm. Participants must be seated with back support, and measurements should be taken after 5 minutes of rest, leaving at least 2 minutes between repetitions.

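### The Aim 1 selection rule does not name age as a model term, so in children aged 6 to 13 some predictors can look associated with blood pressure and unreferenced body measures only because both change with age

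*Protocol article*

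**What the plan says.** The Statistical Analysis section of the protocol article sets out the Aim 1 models in some detail.

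- **Outcomes and target:** "potential baseline associations of dependent variables (eg, anthropometrics and blood pressure) with independent behavioral variables". The outcomes are given as examples, and their scale (raw, percentile or z score) is not stated.
- **Predictors:** also given as examples, "eg, dietary intakes, exercise and sleep time, family interaction, psychosocial well-being, and perception of childhood obesity".
- **First step:** these associations "will be tested using multiple linear regression, starting with univariate regression", with entry at P<.2 and biological plausibility.
- **Second step:** "Models will be built by a combination of univariate analysis and forward stepwise model selection", at P≤.05 and again biological plausibility.
- **Checks:** interactions at P≤.1 "between sex and other variables included in the model", collinearity, and residual plots.

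No covariate is named as fixed. Age appears in the same section only in the separate tests of baseline differences. The sentence about including covariates as appropriate belongs to the Aim 3 mixed models and does not name age.

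The Participants section admits "students aged 6 to 13 years enrolled in the selected schools". Under Blood Pressure the article says "Measurements will be taken in triplicate on the left arm" and gives no reference by age, sex or height. By contrast, BMI and body fat percentiles and a 90th-percentile waist class are derived in the anthropometric sections. Weight has no age reference. Waist-to-height ratio and fat mass index have sex-specific cutoffs, but these are not graded by age.

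**The concern.** Between 6 and 13 years, blood pressure and body size rise with growth. Sleep time and questionnaire responses may also shift with age. The document itself ties one predictor to age: the psychosocial questionnaire comes in two versions split by age group, so pooled scores mix instruments along the age axis. If age is left out, a predictor with no relation to the outcome among children of the same age still has a marginal correlation with it. A univariate screen followed by forward selection tends to pick up such correlations.

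Aim 1 is a stated specific aim. What is at stake is that age-driven associations, for example of shorter sleep with higher blood pressure, are reported as associations with behavior or family setting.

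**Working it through.** The document states no error rate, power or sample size calculation for Aim 1, so there is no figure of its own to reproduce. The school counts in Table 3 do add up: 173 + 117 + 86 + 75 = 451.

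**Inputs from the document.** n = 451; screen at P<.2; entry at P≤.05 (two-sided assumed).

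**Assumptions, not in the document.** Correlation of age with the outcome and of age with the behavior, 0.2 to 0.4 each; independent children; linear relations; age not in the model. For predictors collected only in grades 4 to 6, n = 225 is assumed (about half of 451), because the split by grade is not given.

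**Single behavior with no effect given age.**

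1. The age-induced correlation is r = r(age, outcome) × r(age, behavior).
2. By Fisher's z, m = atanh(r) × √(n − 3), and the chance of significance is Φ(m − c) + Φ(−m − c), with c = 1.960 for P≤.05 and 1.282 for P<.2.
3. Example at 0.4 and 0.3: r = 0.12, atanh(0.12) = 0.1206, √448 = 21.17, m = 2.55. Then Φ(2.55 − 1.96) = Φ(0.59) ≈ 0.72; the other tail is negligible.

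| Age correlations (outcome, behavior) | r | n=451: P<.2 | n=451: P≤.05 | n=225: P≤.05 |
|---|---|---|---|---|
| 0.2, 0.2 | 0.04 | 34.9% | 13.5% | 9.2% |
| 0.3, 0.3 | 0.09 | 73.6% | 48.0% | 27.0% |
| 0.4, 0.3 | 0.12 | 89.8% | 72.3% | 43.5% |
| 0.4, 0.4 | 0.16 | 98.4% | 92.7% | 67.2% |

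The nominal values are 20% and 5%. The n=225 column keeps the same correlations. Within grades 4 to 6 the age span is narrower, so the correlations would probably be smaller and the rates lower still.

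**The two-step rule, simulated.** Each of 600 runs per setting had six behaviors with no effect given age, three of them related to age. The rule was applied without the plausibility criterion, which cannot be simulated. The table shows how often at least one of the three age-related behaviors was selected at n = 451. The nominal value is 1 − 0.95³ ≈ 14%.

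| Age correlations | Age absent | Age offered as a candidate | Age held in every step |
|---|---|---|---|
| 0.2, 0.2 | 36.8% | 13.3% | 16.5% |
| 0.3, 0.3 | 83.7% | 8.0% | 14.5% |
| 0.4, 0.3 | 96.8% | 9.2% | 17.2% |
| 0.4, 0.4 | 100% | 11.8% | 15.3% |

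When the outcome has no correlation with age, as a valid age- and sex-specific percentile should not, the rate with age absent was 13.0%, which is nominal.

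**The case against.** Several points on the other side are sound and limit the finding.

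- **Body measures.** A reader might infer that all body measures enter unstandardized. The document does not support this: it derives BMI and body fat percentiles and a waist percentile class. What it leaves open is which version is the Aim 1 outcome, and that silence is not a statement that raw values are used.
- **Age range.** A reader might infer that every Aim 1 model pools ages 6 to 13. The 24-hour recalls and the physical activity recall are limited to grades 4 to 6, so models with those predictors use fewer children and a narrower age span.
- **Selection rule.** A reader might infer selection by P value alone, with age shut out. Biological plausibility is a joint criterion at both steps, and the predictor list is given as examples, so an analyst could offer age. The simulation shows that offering it already removes most of the false selection. The operative defect is therefore that age is not named at all, more than that it is not forced.
- **Level of detail.** The exact adjustment set of an exploratory baseline regression is often left to a fuller plan. Here, however, the article fixes the model-building rule down to its thresholds and gives age only a descriptive role. The rule is written for behavioral variables, which age is not. Plausibility is also weak protection, since a confounded association between sleep and blood pressure is itself plausible.
- **Size.** The correlations are assumed, and the calculation treats children as independent. Students sit in 24 classrooms paired by grade, and the section says that all analyses will account for clustering. If that covers Aim 1, the rates above are too high, by an amount the document does not allow one to compute.

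**Conclusion.** The concern holds in a limited form. Followed as written, the Aim 1 rule gives no assurance that age is in the model. Blood pressure, weight, waist-to-height ratio and fat mass index have no age reference to compensate. The exposure is clearest for these outcomes against predictors with no stated limit to the upper grades: sleep, family interaction, psychosocial well-being and perception. It is smaller for diet and physical activity. It does not arise where the BMI or body fat percentile is the outcome, provided that the percentile is in fact free of age in this sample.

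With age absent, assumed age correlations of 0.2 to 0.4 on each side and no clustering, a behavior with no effect given age reaches P≤.05 in 13.5% to 93% of samples of 451. The width of that range reflects unknown correlations. It shows what can happen and does not show that any Aim 1 association will be spurious.

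A reader might also infer that the trial's effect estimates are compromised. They are not: Aim 3 compares randomized arms with separate mixed models, and this point concerns the baseline Aim 1 analysis only.

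**What to change.** In the Aim 1 paragraph of Statistical Analysis:

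1. Hold age (continuous) and sex in every model, including the first one-predictor screen.
2. For blood pressure, also hold height, or use values referenced to age, sex and height as the outcome.
3. State the scale of each outcome, and use the percentiles already derived where they exist.
4. Apply the P-value and plausibility selection only to the remaining predictors.

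Age, sex and height are available, so no new data are needed. The cost is two degrees of freedom per model, or three for blood pressure with height, out of 451 children (fewer in models limited to grades 4 to 6). Table 3 marks data analysis as done for two of the four schools and interpretation for none, so the change can still be made before Aim 1 is interpreted. Any Aim 1 models already fitted would need to be rerun.

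### Baseline tests and aim 1 regressions carry no classroom or school term, so P values are too small for location, grade and age; most child-level aim 1 predictors are little affected

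*Protocol article*

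**What the plan says.** All of this is in the protocol article, mainly under Statistical Analysis.

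- Baseline: "To test age, sex, socioeconomic status, and location baseline differences, we will use chi-square tests for qualitative demographic variables", with ANCOVA for the quantitative variables.
- Aim 1: associations of anthropometrics and blood pressure with behavioral variables "will be tested using multiple linear regression, starting with univariate regression" at P<.2. After that, "Models will be built by a combination of univariate analysis and forward stepwise model selection", with entry at P≤.05 and biological plausibility considered at both steps. The predictors given as examples are "dietary intakes, exercise and sleep time, family interaction, psychosocial well-being, and perception of childhood obesity".
- Aim 1 model checks: interactions with sex, collinearity, and checks "for linear regression assumptions (linearity, normality, and homoscedasticity) using residual plots". Independence of observations is not on the list.
- Aim 3: "intervention effects will be evaluated using multilevel mixed-effects regression models", with random effects for classroom and school.
- Within the aim 3 text: "all analyses will account for clustering to provide valid inferences".

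The Abstract makes the same split: chi-square, ANCOVA and multiple linear regression at baseline, and multilevel models for changes between arms. On structure, Selection of Schools states: "Across the 4 schools, a total of 24 classrooms will be included". It also says that classrooms are paired by grade, and that one school represents the rural area and three the urban area.

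**The concern.** Children in the same classroom or school tend to resemble one another. Chi-square tests, ANCOVA and ordinary regression without a cluster term use the number of children as the amount of information. For a factor that differs mainly between classrooms or schools, the information is closer to the number of clusters, and the standard error comes out too small.

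Two of the four baseline factors are of this kind. Location is constant within a school, so the rural side of the contrast is a single cluster. Age follows grade, and classrooms are grade-based. A difference between one rural school and three urban ones could be declared significant when it reflects no more than ordinary variation between schools.

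Aim 1 is one of the three specific aims, and its associations may be read as risk factors. The stepwise rule is a separate weakness: its P values are calculated as if the final model had been fixed in advance.

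**Working it through.** **Inputs from the article.** Results, Table 3: 173 + 117 + 86 + 75 = 451 children in 4 schools, which agrees with the stated total. Selection of Schools: 24 classrooms. Mean classroom size m = 451/24 = 18.8. Significance level .05, taken as two-sided. The article gives no ICC, so every ICC below is an assumption, and there is no stated figure to reproduce.

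**Formulas.**
- Classroom-level factor: design effect D = 1 + (m − 1) × ICC_y.
- Factor that also varies within classrooms: D = 1 + (m − 1) × ICC_y × ICC_x.
- True error of the unadjusted test: 2 × [1 − Φ(1.96/√D)].

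**Classroom-level factor (for example grade).**

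| Outcome ICC (classroom) | D | True error |
|---|---|---|
| 0.01 | 1 + 17.8 × 0.01 = 1.18 | 0.071 |
| 0.02 | 1.36 | 0.092 |
| 0.05 | 1.89 | 0.154 |
| 0.10 | 2.78 | 0.240 |

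Age is nearly classroom-level. With an assumed predictor ICC of 0.9 and outcome ICC of 0.05, D = 1 + 17.8 × 0.9 × 0.05 = 1.80 and true error is 0.144, against 0.154 for grade.

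**Location.** With a school random effect of ICC r, the variance of the rural–urban difference is r × (1 + Σn_j²/n_u²) + (1 − r) × (1/n_r + 1/n_u). Here n_r is the size of the rural school, n_j are the sizes of the three urban schools, and n_u is their sum. D is this variance divided by (1/n_r + 1/n_u). Table 3 does not show which school is rural, so each was tried in turn.

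Worked case, rural n = 173: n_u = 278, Σn_j²/n_u² = 26,710/77,284 = 0.346, and 1/173 + 1/278 = 0.00938. At r = 0.005, D = (0.005 × 1.346 + 0.995 × 0.00938)/0.00938 = 1.71 and true error is 0.134.

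| School ICC | D (range over the rural school) | True error |
|---|---|---|
| 0.005 | 1.42–1.71 | 0.10–0.13 |
| 0.01 | 1.84–2.42 | 0.15–0.21 |
| 0.02 | 2.68–3.85 | 0.23–0.32 |
| 0.05 | 5.20–8.12 | 0.39–0.49 |

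**Child-level aim 1 predictors.** With outcome ICC 0.01 to 0.10, true error is 0.051–0.060 for a predictor ICC of 0.05 and 0.054–0.092 for a predictor ICC of 0.2. With no between-classroom variation in the predictor, D = 1 and there is no inflation; sex would be such a case if evenly spread over classrooms.

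**Stepwise rule.** With k independent null candidates, the chance that at least one has P≤.05 is 1 − 0.95^k: 0.265 for 6, 0.401 for 10, 0.642 for 20. Simulating the P<.2 screen and forward entry with 451 children and no clustering gave 0.266 for 6 and 0.392 for 10. A further simulation (3,000 runs) set the stepwise rule beside a single pre-listed model. At least one P≤.05 occurred in 38.6% against 38.1% of runs with 10 candidates, and in 62.2% against 62.4% with 20. The number of candidates is not stated, and the simulations leave out the biological plausibility condition.

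**The case against.** **The contradiction may be only literal.** The promise about all analyses opens with the cluster-based allocation and stands between sentences on the aim 3 model, so it is naturally read as covering the arm comparisons. This stands: a reader might infer a flat self-contradiction, and the text does not compel that. But on the narrow reading the baseline tests and aim 1 have no stated adjustment, and on the literal reading the methods named do not deliver what is promised. The wording needs repair either way.

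**A condensed article may leave the adjustment to a fuller plan.** That would answer a missing detail. Here the article names specific methods, and its list of assumptions to check omits independence. That the children are treated as independent remains an inference from the tests named.

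**Most aim 1 predictors vary between children.** This stands. A reader might infer that all these P values are materially too small, and the arithmetic does not support that. Nor does the article support assuming that recalls cluster by classroom, since it describes individual interviews, or that socioeconomic level varies mainly between classrooms.

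**The stepwise figures do not show damage from selection.** This also stands. A reader might take a 40% or 64% chance of a false finding as the price of stepwise selection. It is ordinary multiplicity, and a pre-listed model has practically the same rate. Stepwise selection also has no bearing on the clustering promise.

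**Aim 1 is a baseline question.** Correct: no estimate of the intervention effect depends on it.

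**Conclusion.** The point holds for the baseline tests by location and by age, and for any aim 1 predictor that varies mainly between classrooms or schools. Location is the strongest case: with a school ICC of only 0.01, an unadjusted test errs 15% to 21% of the time instead of 5%. For most child-level aim 1 predictors the effect is small, and the aim 3 comparison already has classroom and school random effects.

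The sizes rest on assumed ICCs, roughly equal classroom sizes and a normal approximation. The location figures allow for variation between schools only. Diet recalls and the physical activity recall are limited to grades 4 to 6, so models using them have fewer than 451 children and fewer than 24 classrooms, and the figures do not carry over to them exactly.

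Post-selection P values and intervals in aim 1 cannot be taken at face value because they ignore the selection. That is a secondary point about reporting, and the calculations here do not put a size on it.

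**What to change.** 1. Fit the baseline comparisons and aim 1 as linear or logistic mixed models with a classroom random intercept and fixed school effects. Four schools are too few for cluster-robust standard errors by school to be reliable.
2. Report rural versus urban descriptively. With one rural school, location cannot be separated from that school, and the fixed school effects absorb the contrast.
3. For aim 1, list the predictors for each outcome in advance and report all coefficients with 95% CIs, or label the results exploratory. This makes the selection visible but does not by itself reduce the multiplicity.
4. Make the clustering sentence match. If the sponsor keeps the present methods, limit that sentence to aim 3 and state that baseline and aim 1 P values are not adjusted for clustering or selection.

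The cost is a change to the analysis text and rerunning any baseline work already done: Table 3 marks data analysis complete for two of the four schools and interpretation for none. Some associations will lose nominal significance, and rural versus urban will no longer be tested.
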